#### 13.2 Analysis set

The following groups are defined as the analysis sets. The acceptance or rejection of individual patients in each group is determined prior to the fixing of the data as needed. The main analysis set for efficacy evaluation is set as the “efficacy analysis set,” but a similar efficacy analysis is implemented for “ACS.”

### 13.2.1 Safety set

All patients who received darbepoetin alfa are included in the safety set.

### 13.2.2 Efficacy analysis set

The group excluding the following patients from the safety set is defined as the efficacy analysis set.

- Those who were ineligible after registration
- Those who discontinued darbepoetin alfa administration within 12 weeks after the start of treatment
- Those who do not have a single DA administration record 12 weeks after the start of treatment
- Hb concentration measurements are not obtained at the start of treatment and at 12 weeks

### 13.2.3 Administration Algorithm Compliance Set

The group that complied with the “Recommended darbepoetin alfa administration method” shown in Section 8.1.2, among the efficacy analysis set, is defined as the ACS.

## 13.3 Analysis items / methods

As a general rule, categorical data calculate frequencies and percentages, and continuous values are summarized with the summary statistical values of the number of patients, average value, standard deviation, minimum value, median value, and maximum value.

A significance level is not set because there are no hypotheses to be verified that are set in this research, but a two-sided P-value of 5% is set when using statistical test methods in an exploratory manner.

Details on analyses not recorded in this research protocol are described in the “Statistical Analysis Plan”

### 13.3.1 Renal function deterioration, CVD event investigation

A proportional hazards model that includes the following covariates is applied, and the factors that affect event occurrence are investigated. Covariates are added or decreased as required for the investigation of the model. Hb concentration values at each measurement time point up to 24 weeks instead of week 12 of administration are also investigated. The presence of diabetic complications, arteriosclerosis, and chronic inflammation should also be considered as stratification factors. These analyses are used to investigate the prediction equation for event occurrence from the covariates.

- Age; sex; weight; eGFR, serum albumin, hemoglobin concentration, high-sensitive CRP, NT-pro BNP, folic acid, vitamin B12, serum iron, serum ferritin, and TSAT 12 weeks after the start of treatment; the presence of diabetic complications, arteriosclerosis, chronic inflammation, malignant tumor complications, hemorrhagic lesion complications, collagen disease and rheumatic disease complications, concomitant immunosuppressant or steroid use, and other myelosuppressive factors; and the darbepoetin alfa administered dose (total administered dose, administered dose 12 weeks after the start of treatment).

Next, the cut-off values of each ERI are gradually increased from the minimum value to the maximum

value; a time-dependent ROC curve of the survival time data with censoring is created, and the AUC is compared. If the cut-off value is set from the ROC curves of each obtained ERI, then these are divided into two groups at the cut-off value, Kaplan-Meier plots are created, and the annual event occurrence rate (human-year method) and 95% confidence intervals are estimated. The cut-off values of the ERIs may also be investigated using the cross-validation method, if considered useful.

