### 5.2 Exclusion criteria

- 1) Patients who plan to initiate maintenance dialysis or have a kidney transplant within 24 weeks after registration
- 2) Patients with malignant tumors, blood disorders, or obvious hemorrhagic lesions
- 3) Patients with hypersensitivity to ESA components or to ESA
- 4) Pregnant women, lactating women, patients who may be pregnant, or patients wishing to become pregnant during the research period
- 5) Patients participating in other clinical trials
- 6) Other patients deemed inappropriate for this research by the lead principal physician or study physician

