|     |                                                             | Blood transfusion amount                                                                                                                                                                                                                                              |                                                                                                                                                                           |                                                                                                                                                                                                                                                                                                                                                                                                                                |
| 9   | Development of factors that affect anemia                   | Malignant tumors, hemorrhagic lesions, collagen disease and rheumatic disease, immunosuppressant or steroid use (apply “2. Concomitant drug usage status” data correspondingly), other myelosuppressive factors (details)
Note) refer to attachment for definition |                                                                                                                                                                           |                                                                                                                                                                                                                                                                                                                                                                                                                                |

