## 12. Definition of endpoints

### 12.1 Primary endpoints

#### 12.1.1 Renal function deterioration

Composite events of each event occurring 12 weeks after the start of treatment (see “10.4.1 Event – Renal function deterioration”) are set as renal function deterioration. The number of days until occurrence is calculated, with 12 weeks after the start of treatment as the starting point.

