### 12.3 ERI

The following five indices are considered new candidates for the ESA response indices (ERIs) to be investigated.

- ERI-1A (index according to one time point at 12 weeks)

$$\frac{\text{DA administered dose 12 weeks after the start of treatment (}\mu\text{g)}}{\text{Hb concentration 12 weeks after the start of treatment (g/dL)} \times \text{weight 12 weeks after the start of treatment (kg)}}$$

- ERI-1B (index according to one time point at 12 weeks)

$$\frac{\text{DA administered dose 12 weeks after the start of treatment (}\mu\text{g)}}{\text{Hb concentration 12 weeks after the start of treatment (g/dL)}}$$

- ERI-2A (index that considers the cumulative administered dose up to 12 weeks and changes in Hb concentration)

$$\frac{\text{Total DA administered dose up to 12 weeks after the start of treatment } (\mu\text{g})}{\text{Amount of change} \times \text{weight at 12 weeks (kg)}}$$

- ERI-2B (index that considers the cumulative administered dose up to 12 weeks and changes in Hb concentration)

$$\frac{\text{Total DA administered dose up to 12 weeks after the start of treatment } (\mu\text{g})}{\text{Amount of change}}$$

- Change in Hb concentration (changes in Hb concentration up to 12 weeks)

$$\text{Hb concentration at 12 weeks (g/dL)} - \text{prior Hb concentration (g/dL)}$$

A similar index is created for the ERI index from the Hb concentration and darbepoetin alfa administered at 16 weeks and at 24 weeks in addition to that at 12 weeks, and the associations between these indices and event occurrence are also investigated. When the ERI index at 12 weeks favorably predicts event occurrence, then whether the ERI index composed of the values at week 10, 8, 6, 4, and 2 favorably predicted the event occurrence is confirmed in order.

New indices are further explored if no associations between these index candidates and renal function deterioration or CVD events were found.

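### Section 13.3.1 models events counted from week 12 but sets no time limit on total dose or on the anemia factors, so whole-follow-up values could enter as fixed covariates

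*Protocol*

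**What the plan says.** For renal function deterioration, Protocol 12.1.1 counts "Composite events of each event occurring 12 weeks after the start of treatment" and adds: "The number of days until occurrence is calculated, with 12 weeks after the start of treatment as the starting point". Section 12.1.2 does the same for CVD events.

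Section 13.3.1 lists the covariates of the proportional hazards model. They fall into three groups by timing:

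- The laboratory values are dated; the list closes with "serum ferritin, and TSAT 12 weeks after the start of treatment".
- The dose term is "the darbepoetin alfa administered dose (total administered dose, administered dose 12 weeks after the start of treatment". Its second part is dated and its first part is not.
- The clinical factors carry no date. They include "malignant tumor complications, hemorrhagic lesion complications, collagen disease and rheumatic disease complications", immunosuppressant or steroid use, and other myelosuppressive factors.

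Elsewhere the protocol does bound a cumulative dose: the numerator of ERI-2A and ERI-2B in 12.3 is "Total DA administered dose up to 12 weeks after the start of treatment".

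Two of the undated factors are barred at entry, since 5.2 excludes "Patients with malignant tumors, blood disorders, or obvious hemorrhagic lesions". Item 9 of the follow-up form in 10.1.3, "Development of factors that affect anemia", is collected from the start of treatment to week 96. Under 8.1, darbepoetin dosing in the study also runs until just before week 96.

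**The concern.** A fixed covariate in a survival model should be known at the time origin, here week 12. If a covariate is accumulated over all of follow-up, patients who have the event early and whose records then stop have had less time to accumulate dose or to acquire a factor. The covariate then partly measures how long the patient stayed event-free, which is immortal-time bias. With no true effect it makes dose or factor look protective.

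The model is meant to identify factors that affect events and to yield a prediction equation. An equation that needs a total dose from after week 12 could not be applied at week 12. Tumor and hemorrhagic lesion are the most exposed factors: because they are excluded at entry, they vary mainly through later onset.

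**Working it through.** **Inputs from the protocol.** N = 2,000 (11.1); 13.1 events per 100 person-years (13.1); time origin week 12 (12.1); observation to week 96, hence 84 weeks at risk.

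**The plan's own figure.** 2,000 × 2 years × 0.131 = 524 events. 524 ± 1.96 × √524 = 479.1 to 568.9, which reproduces the stated 480–568. The protocol gives no figure for the covariate question.

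**Hand illustration.** Take 30 µg every two weeks, the usual initial dose in the 8.1.2 excerpt, held constant for two patients. One has an event at week 20 and the records stop there; the other is event-free throughout.

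- Total to week 12 (weeks 0, 2, …, 12): 7 × 30 = 210 µg for both.
- Total to the end of records: 11 × 30 = 330 µg for the first (weeks 0 to 20) and 48 × 30 = 1,440 µg for the second (weeks 0 to 94).

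Dosing is identical, yet the undated total differs by a factor of 1,440/330 = 4.4.

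**Null simulations.** Events are exponential at 0.131 per year from week 12, unrelated to dose or factor, so the true HR is 1.00. Expected first events: 2,000 × (1 − exp(−0.131 × 84/52)) = about 381; simulation A gave 382–383. Each Cox model has one covariate. Assumptions not in the documents:

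- Simulation A (60 replicates): two-weekly dose log-normal, median 40 µg, log-SD 0.5; factor onset 2, 5 or 10% per year; share of event patients whose dosing and records run on to week 96 set at 0, 50, 80 or 100%.
- Simulation B (100 replicates per setting): log-normal dose, median 45 µg; 5% per year dropout; factor onset 3–10 per 100 person-years; records stop at the event, or run on after the 70% of events taken as non-fatal.

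| Event patients whose records run on | HR per SD, whole-follow-up dose | HR, factor ever present |
|---|---|---|
| None | 0.15–0.16 (A), about 0.21 (B) | 0.53–0.56 (A), 0.46–0.50 (B) |
| 50% | 0.55 (A) | 0.78 (A) |
| 70% | about 0.77 (B) | 0.80–0.85 (B) |
| 80% | 0.82 (A) | 0.86 (A) |
| All | 0.99 (A) | 0.99 (A) |

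With dose cut at week 12, the HR per SD is 0.98–1.00 in both simulations. With the factor cut at week 12, it is 0.91–1.00 in the settings of A where every replicate could be estimated; the other settings were too sparse.

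**Which row applies.** Section 8.2 continues observation after dialysis or transplant as far as possible, and 10.1.5 continues it after an event if the patient can be traced. The CVD composite in 10.4.1 includes deaths, so its last row cannot be reached. The renal composite has no fatal component and could come close to it.

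**The case against.** The strongest reply is that week 12 is the natural reading. The two dose terms in 13.3.1 match the numerators in 12.3: dose at week 12 for ERI-1, cumulative dose to week 12 for ERI-2. So 13.3.1 may simply abbreviate. Where that section departs from week 12 it says so, for Hb values up to week 24, which suggests that week 12 is the default. Covariate derivation is also common SAP content, and that document is not at hand.

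Much of this stands. A reader might infer that the protocol builds these covariates from records up to week 96; nothing in it says so. But 13.3.1 does fix this model, dates some covariates and leaves others open. Its Hb provision also admits values from after the time origin, so a silent week-12 default cannot be relied on.

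A reader might also infer that all the anemia factors can arise only after entry. That is not supported. Immunosuppressant or steroid use and collagen or rheumatic disease are not excluded and have start-of-treatment records. The pre-treatment history in 10.1.2 includes existing malignant tumor, and the schedule in 0.7 requires the anemia factors at the start and through week 12. A week-12 derivation is therefore feasible.

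Finally, the extreme hazard ratios require records to end at the event, whereas 8.2 and 10.1.5 keep many patients under observation. That is correct, and it shrinks the bias.

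**Conclusion.** The point holds as a gap in what 13.3.1 fixes: the text permits, but does not require, fixed covariates built from information after time zero. If they were built that way and there were no true effect, the HR per SD for dose would be about 0.15–0.21 with records stopping at the event, 0.55–0.82 with 50–80% running on, and 0.99 with all running on. For an ever-present factor it would be about 0.46–0.56, 0.78–0.86 and 0.99. The bias is likely largest for the CVD composite and may be small for the renal one.

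These sizes rest on the assumed dose distribution, onset rates and post-event recording, and on one-covariate models. The net sign in real data is not assured: poor responders may be given more drug and also be at higher risk, which pushes the other way. A reader might therefore conclude that the high-dose question in section 2 would come out reversed; the documents and calculations do not support that.

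Nor should the point be carried to 13.3.2, although it reuses the covariates. That is a mixed model of eGFR from the start of administration; it was not examined here, and a week-12 total would still post-date the earliest eGFR values. The week-12 ERI candidates in 12.3 are already bounded and are unaffected.

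**What to change.** In 13.3.1, bound the total dose with the wording that 12.3 already uses ("Total DA administered dose up to 12 weeks after the start of treatment"). State that tumor, hemorrhagic lesion, collagen or rheumatic disease, immunosuppressant or steroid use and other myelosuppressive factors are derived from records up to week 12. Allow later onset or later dose only as a time-dependent covariate that changes at its recorded date. Mirror this in the SAP.

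The cost is one sentence and no new data; if week 12 was always intended, nothing changes in the analysis.

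The downside is sparse factors. With an assumed onset of 5% per year, about 2,000 × (1 − exp(−0.05 × 12/52)) = 23 patients have the factor by week 12. With about 19% having an event (381/2,000), that is some 4.4 events. The SE of the log HR is then roughly √(1/4.4 + 1/377) = 0.48, so the 95% interval spans a factor of about 2.6 either way. At 2% and 10% per year the counts are about 9 and 46 patients. Those coefficients will be imprecise, and the plan should say so.

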
Therefore, a multicenter prospective observational study of CKD patients who were not administered ESA and where darbepoetin alfa administration was planned was conducted with the research objective

of using darbepoetin alfa, which is an ESA that is widely used in renal anemia treatment among CKD patients with renal anemia, to collect a wide range of clinical information obtained from the initial stage of ESA treatment and investigate the actual conditions of patients with low response to darbepoetin alfa and factors associated with low response, as well as propose evaluation indices for low ESA response and cut-off values of related factors according to Japanese medical practice.

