#### 11. Sample size and research period

##### 11.1 Sample size

The sample size is 2,000 patients.

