### 13. Statistical analysis

#### 13.1 Rationale for the sample size design

The objective of this research is to clarify the actual conditions of low ESA response cases in Japan, investigate factors related to low ESA response cases, and search for new ERIs. Therefore, in consideration of securing data for each type of exploratory analysis, a sample size of 2,000 was set as the scale of research where evaluations of low ESA response cases were thought to be possible.

The TREAT trial conducted internationally reported that renal events (end-stage renal failure or death) in the darbepoetin alfa group and the two-year occurrence rate of CVD events was approximately 23%–24%. If the event occurrence rate was set as 13.1 / 100 people/year from this result, then the number of events observed in two years with a sample size of 2,000 would be 480–568 patients at a 95% confidence interval, which is thought to be a sufficient number of events for the planned analyses.

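### ERI cut-offs are set from the ROC curve and then described by Kaplan-Meier curves and event rates in the same patients, with validation optional, so the separation is overstated and the intervals ignore the search

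*Protocol*

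**What the plan says.** Section 13.3.1 moves the threshold of each ERI across its whole range, builds a time-dependent ROC curve and compares the AUCs. If a cut-off is set from a curve, "then these are divided into two groups at the cut-off value, Kaplan-Meier plots are created, and the annual event occurrence rate (human-year method") is estimated with 95% confidence intervals. No other set of patients is named for this step. The only safeguard is this sentence: "The cut-off values of the ERIs may also be investigated using the cross-validation method, if considered useful".

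Section 12.3 sets the breadth of the search. It lists five candidate indices at week 12, repeats similar indices at weeks 16 and 24, and goes back through weeks 10 to 2 if the week-12 index predicts well. It adds: "New indices are further explored if no associations between these index candidates and renal function deterioration or CVD events were found". Section 12.1 has two primary endpoints, renal function deterioration and CVD events.

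Section 2 states the intended product, which is to "propose evaluation indices for low ESA response and cut-off values of related factors according to Japanese medical practice". Section 13.3 sets no significance level because no hypothesis is to be verified, but says that "a two-sided P-value of 5% is set when using statistical test methods in an exploratory manner".

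**The concern.** A cut-off chosen because it separates events from non-events in a data set will separate them less well in new patients. Ordinary 95% intervals for the two groups' rates treat the cut-off, and the index it belongs to, as fixed beforehand. Here both come from the data that supply the rates.

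The one safeguard may be skipped. If used, it covers the cut-off but not the choice among indices, weeks and endpoints. Because further indices are sought when none is associated, the search has no stated stopping point.

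At stake is the main product of the study. A cut-off offered for practice would carry an exaggerated contrast between high and low groups and intervals that are too narrow. An index with no prognostic value could look useful.

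**Working it through.** **Inputs from the protocol.** Section 11.1: "The sample size is 2,000 patients". Section 13.1: "If the event occurrence rate was set as 13.1 / 100 people/year from this result", and "the number of events observed in two years with a sample size of 2,000 would be 480–568 patients at a 95% confidence interval".

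**The plan's own figure.** 2,000 × 2 × 0.131 = 524 events, and 524 ± 1.96 × √524 = 479.1 to 568.9. Rounded inward this is 480–568, so it is reproduced. The rate follows from 23% at two years: −ln(0.77)/2 = 0.1307 per year. Counting first events only, the simulated studies average 2,000 × (1 − e^(−0.262)) = 461.

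**Assumptions not in the protocol.**
- The ROC rule is Youden: choose c to maximise J(c) = sensitivity(c) − [1 − specificity(c)].
- The direction is either fixed (high ERI = worse, maximise J) or free (maximise |J|).
- Cut-offs are either unrestricted or kept within the 5th–95th or 10th–90th percentile.
- Event times are exponential. Follow-up is two years or 84 weeks (96 − 12, since time counts from week 12).
- For five indices, the pairwise correlation is 0.6 to 0.9.

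**Measures**, with d events and T person-years in each group:
- Group comparison: log-rank test, or log rate ratio ln[(d₁/T₁)/(d₀/T₀)] with standard error √(1/d₁ + 1/d₀).
- Reported intervals: ln(d/T) ± 1.96/√d in each group, checked for non-overlap. With equal event counts, non-overlap needs |z| > 1.96 × √2 = 2.77, which has a chance probability of about 0.6%. It is a much stricter criterion than p<0.05.

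**Results for indices unrelated to outcome** (1,000 to 2,000 simulated studies per setting):

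| Setting | Groups differ at p<0.05 | Reported intervals do not overlap |
|---|---|---|
| Cut-off fixed in advance at the median | 4.5% | – |
| Cut-off chosen in one half, tested in the other | 4.7% | – |
| One index, direction fixed | about 20–28% | about 6–12%, both directions together |
| One index, direction free | about 42–45% | (as above) |
| Five indices, direction fixed | about 42–62% | about 10–27%, both directions together |
| Five indices, direction free | about 70–92% | (as above) |

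For one index the median spurious rate ratio is 1.16 to 1.24. With 1,500 patients the one-index range is 23–44%. At 5 events per 100 person-years over 84 weeks it is 20–39%.

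The five-index range depends on the selection rule and the correlation. With fixed direction and correlation 0.6, the index with the best ROC separation differs in 53–55% of studies, and at least one of the five in 59%. At correlation 0.9 the corresponding figures are 42–45% and 47–51%.

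**A weak but real index** (hazard ratio 1.105 per SD): the apparent rate ratio averages 1.33, against 1.18 when the same cut-off is applied to new patients. A true signal is overstated too.

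**Does cross-validation restore calibration?** Two-fold cross-validated groups differ at p<0.05 in 5.9% of null studies. Pooled ten-fold groups show the high group as worse in 6.0%, against a nominal 2.5% in that direction. Pooled folds therefore remove most of the bias but do not give a valid p-value unaided.

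**The case against.** **The study is exploratory and names no test between the two groups.** This is correct. Section 13.3.1 plans curves and rates with intervals, not a log-rank or rate-ratio test. The p<0.05 figures describe what a reader would find on comparing the groups. On what is actually reported, two separate intervals, the false signal is much smaller. But exploratory status does not make an interval valid after a search, and section 2 intends the cut-offs for practice.

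**The direction is given by the premise.** Section 2 links low response to poor prognosis, and for ERI-1A and ERI-1B more drug per unit of Hb means lower response. The fixed-direction figures are therefore the fairer ones for those indices. Direction is less clear for ERI-2A and ERI-2B, which change sign when the Hb change is negative, so the free-direction figures are not irrelevant.

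**Moving the threshold is simply how a ROC curve is drawn.** A reader might infer that the AUC comparison is inflated by the cut-off search. It is not: AUC uses the whole index. It is optimistic only through choosing the best of several indices.

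**The SAP may require validation.** It may; it is not shown. But section 13.3 leaves to the SAP the detail of analyses that the protocol does not record. This analysis is recorded, and its validation is stated as optional.

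**Conclusion.** The point stands. As written, section 13.3.1 overstates the separation between ERI groups, and its intervals ignore the search over cut-offs and indices. A comparison of the groups formed from one useless index would mislead several times more often than the nominal 5%, at a spurious rate ratio near 1.2, and more often again with five indices. By the stricter standard of non-overlapping intervals the problem is smaller but still present.

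A reader might infer that a useless index would nearly always be put forward, since figures around 90% can be produced. The documents do not support that. Those figures need free choice of direction, an assumed correlation of about 0.6 and a formal group test that the protocol does not plan.

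The existence and direction of the bias follow from the text. Its size rests on the assumed ROC rule, direction, trimming and correlation, so it is a range and not a single figure.

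**What to change.** In section 13.3.1:
- Make internal validation mandatory, with the choice of index and of cut-off repeated inside every bootstrap sample or cross-validation fold.
- Report the optimism-corrected AUC, together with optimism-corrected group rates or curves from out-of-fold group assignment. Use a permutation reference for any p-value from pooled folds.
- Report the association of each continuous ERI with each endpoint alongside the two-group results.
- Label Kaplan-Meier curves and rates from the same patients as descriptive and not validated.

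In section 12.3, state that any index added later passes through the same procedure and is labelled post hoc.

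No new data are needed. The cost is some computing time, a few lines of text, and reported separation that will look less favourable.
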